### Analysis plans

#### Statistical analysis

Outcomes will be aggregated and analysed at the practice level. The analysis will estimate the effect of each intervention compared with current practice and will also estimate the differential effect between interventions (*i.e.*, inclusion of a text-based intervention, frequency of feedback and inclusion of a comparator). We will perform main effects analyses of covariance on the 12-month prescribing rate, adjusting for the pre-intervention yearly prescribing rate, practice size (single-handed/multi-handed), and the annual number of treatment claims submitted by the practice. The model fitting strategy will test the practice size variable (design), then the pre-intervention prescribing rate (covariate), and lastly a categorical variable (intervention) will be included to correspond with the main effects of the different interventions. The same approach will be used for all prescribing behaviours under investigation.

We will investigate whether larger effects of the interventions are observed for practices reporting higher pre-intervention levels of prescribing (defined as upper quartile practices). Additionally, to test for a reduction in the spread of prescribing levels, we will apply Levene’s test for equality of variances between the pre-intervention and intervention phases.

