### Sample size

The sample size calculation is based on aggregated practice level antibiotic prescribing. There will be 795 practices participating in the trial, of which 632 practices will be randomised to the intervention group. Each of the eight sub-level experimental units in the intervention group will have 79 practices. This is the required sample size to achieve 80% power (with two-sided alpha of 2.5% allowing for multiple comparisons) to detect a 10% difference in overall antibiotic prescribing between intervention groups. This applies to the comparison between A&F only (n = 316) and A&F with a text-based intervention (n = 316), the comparison between feedback at zero, six, and nine months versus zero and six months only and the comparison between those with and without a Health Board comparator. The sample size has been reduced using the correction described by Borm *et al*. for trials with correlated data [18]. The comparison between the control group (n = 163) and the intervention group (n = 632) will have 80% power to detect a 12% decrease in overall antibiotic prescribing.

The sample size calculation is based on prescribing activity recorded in PRISMS for the 1,799 dentist lists in Scotland known to be prescribing throughout the year ending June 2010. The mean number of antibiotic items prescribed per list was 141.1 with an SD of 140.9. The correlation with the year ending June 2009 is 0.91.

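### The planned Levene test of reduced spread treats the same practices' two phases as independent and has no control contrast, so it is conservative and cannot attribute any narrowing to feedback

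*Protocol article*

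**What the plan says.** The last sentence of the protocol's Statistical analysis section adds one analysis of variability. Its purpose is "to test for a reduction in the spread of prescribing levels", and its method is Levene's "test for equality of variances between the pre-intervention and intervention phases". The sentence fixes both the test and the contrast. It does not say which practices enter (intervention only, each arm in turn, or all 795), and it mentions no comparison between randomised groups.

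Two other statements show that the phases are repeated measures on the same units. The same section says "Outcomes will be aggregated and analysed at the practice level", and its ANCOVA works by "adjusting for the pre-intervention yearly prescribing rate", so each practice contributes a value before and a value after. The Sample size section reports "The correlation with the year ending June 2009 is 0.91" and reduces the sample size on the strength of that correlation. It also gives the group sizes: 632 intervention and 163 control practices.

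**The concern.** There are two separate problems.

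1. **Pairing.** Levene's test compares mean absolute deviations as if the two sets came from different units. When practices are positively correlated across phases, the true variance of that difference is smaller than the test assumes. The test then rejects too seldom and loses power. The plan uses the pairing for the mean (ANCOVA and sample size) and ignores it for the variance.

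2. **No randomised contrast.** Any change in spread between the two years counts as a reduction, whatever its cause. The Trial Design section says the control group is there to test whether any form of feedback works, yet the stated spread test makes no use of it as a comparator. The Background reports dental antibiotic use 7.6% higher in 2011 than in 2010. That concerns level, not spread, but it shows that prescribing moves from year to year without this trial.

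Wide variation in prescribing is part of the protocol's stated rationale, so readers will want to interpret this result. A null would say little about modest narrowing, and a positive result could not be credited to feedback.

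**Working it through.** **The plan's own power figure.** The document gives no operating figure for Levene's test, so the check starts from the power statement that uses the same correlation. Inputs: "The mean number of antibiotic items prescribed per list was 141.1 with an SD of 140.9", correlation 0.91, and "80% power (with two-sided alpha of 2.5% allowing for multiple comparisons") "to detect a 10% difference in overall antibiotic prescribing between intervention groups" of 316 each.

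- Adjusted SD = 140.9 × √(1 − 0.91²) = 58.42; difference = 14.11.
- z = 14.11 / (58.42 × √(2/316)) = 3.04; power = Φ(3.04 − 2.24) = 78.7%, in line with the stated 80%. Solving for n gives 326 per group against 316.
- Control comparison, 12% effect: z = 16.93 / (58.42 × √(1/163 + 1/632)) = 3.30; power 85.5% at the same alpha, so the stated 80% is met.

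The 0.91 therefore does the work the protocol says it does.

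**Size of the unpaired test.** Assume normal data, n = 632 pairs, nominal 5%. For correlation r, the correlation of absolute deviations is

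c(r) = (2/π)(√(1 − r²) + r·arcsin r − 1) / (1 − 2/π).

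The Levene statistic then has null SD √(1 − c) instead of 1, and its size is 2Φ(−1.96/√(1 − c)).

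| r | c | √(1 − c) | Size by formula | Size by simulation (3,000 runs) |
|---|---|---|---|---|
| 0 | 0 | 1 | 5% | 4.5% |
| 0.5 | 0.224 | 0.881 | 2.6% | 2.8% |
| 0.7 | 0.450 | 0.742 | 0.8% | 0.8% |
| 0.91 | 0.797 | 0.450 | 0.001% | 0.0% |

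A paired Levene test (one-sample t test on each practice's change in absolute deviation from the phase median) had simulated size of 4.5% to 5.6% throughout. With 795 pairs the pattern was the same.

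**Power at r = 0.91, SD reduced to s times baseline.** The mean difference in absolute deviation is (1 − s)√(2/π).

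- s = 0.95: difference 0.0399. SE assumed by Levene = √(0.3634 × 1.9025/632) = 0.0331. True SE = √(0.3634 × (1.9025 − 1.9 × 0.797)/632) = 0.0149. Levene power = Φ((0.0399 − 1.96 × 0.0331)/0.0149) = about 5% (simulated 4.5%; about 4% in a further run). Paired power = Φ(2.67 − 1.96) = 76% (simulated 75% to 76%).
- s = 0.93: simulated Levene 29%, paired 96%.
- s = 0.90: Levene 87% by formula and by simulation; paired about 100%.

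With skewed (gamma, shape 4) data the planned test again had 0% size. For a 5% smaller SD it had 5% power (mean-centred) or 2% (median-centred), against 69% for the paired Levene, whose size stayed near 5%.

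**Attribution.** Let the SD shrink by 10% in both arms, with no feedback effect. The phase contrast in the intervention arm rejects in 87% of 2,000 runs. A between-arm Levene test on post-period rates rejects in 4.6%.

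**Randomised alternative.** Regress each practice's absolute deviation on arm, adjusting for its baseline absolute deviation, 632 v 163. Simulation gave about 5% size, also under a common 10% shrinkage, and about 72% power for a 10% smaller SD in the intervention arm. By formula: SE = √(0.3634 × (1 − 0.797²) × (0.81/632 + 1/163)) = 0.0313; z = 0.0798/0.0313 = 2.55; power = Φ(2.55 − 1.96) = 72%.

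**The case against.** The other side has several good points.

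- **It is a supplementary analysis.** Spread is not the primary outcome, not one of the five secondary outcomes, not in the research question and not in the sample size calculation. Whether feedback works is answered by the baseline-adjusted ANCOVA with a control group. This stands, and it limits the severity.
- **The test is not powerless.** It detects a 10% smaller SD about 87% of the time at r = 0.91. The large loss is confined to smaller changes. This stands.
- **The correlation is borrowed.** The 0.91 is for item counts per dentist list in the years ending June 2009 and June 2010, whereas the outcome is a practice-level rate per 100 claims. This stands. At 0.5 to 0.7 the loss is milder, though size is already below nominal.
- **The test could be run separately in each arm.** The wording allows it, and the control result would then show secular change descriptively. That is still not a test of the difference between arms.

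A reader might also infer that the error rate is wrong in both directions, because a uniform proportional fall would trigger the raw-scale test. The document does not support that. If every practice falls by 10%, the variance of prescribing levels really is smaller, so rejecting is correct for the hypothesis stated; the sentence speaks of levels, not relative spread. The rejection rate in that scenario also depends on a coefficient of variation that the protocol does not give for practice rates. For lognormal data it was 54% (mean-centred) or 31% (median-centred) at 0.6, and 26% or 5% at 1.0.

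**Conclusion.** The concern holds, at the level of something that should be fixed. The stated test does not suit paired data, and its error is conservative: size of about 3%, 1% and 0% at correlations of 0.5, 0.7 and 0.91, and about 4% power for a 5% smaller SD at 0.91 where a paired version has about 76%. The larger fault is the contrast. Between phases, a common 10% shrinkage in SD would be read as a reduction about 87% of the time with no feedback effect, and only the 163 randomised controls can separate the two.

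The percentages assume 632 practices, normal data (with a gamma check) and a nominal 5% level, since the protocol sets no alpha for this test. The lack of independence and of a randomised contrast does not depend on those assumptions. It would be wrong to infer that the primary result is at risk; the ANCOVA is unaffected.

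**What to change.** Replace the closing sentence of the Statistical analysis section with a between-arm comparison. For each practice, take the absolute deviation of its 12-month rate from its arm's median. Regress this on arm, adjusting for the practice's baseline absolute deviation, with robust standard errors.

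Add a log-rate version as a sensitivity analysis if relative spread is of interest, where zero counts allow; practices with no items may make this impractical for narrow outcomes such as second-line antibiotics.

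If a before-after figure within an arm is still wanted, use the paired Levene test and label it descriptive. It is preferable to the Pitman-Morgan test, whose size rose to 14% to 31% with skewed gamma data while the paired Levene stayed near 5%.

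The cost is a few sentences and a few lines of code, with no extra data. There is a small loss: the randomised contrast has about 72% power for a 10% smaller SD, against about 87% for the planned before-after test, because the control arm has only 163 practices. In return, a positive result can be attributed to feedback.

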### Timing and frequency of analysis

A single principle analysis is anticipated at 12 months post baseline intervention (*i.e.*, covering up to 30 April 2014). The data will be available in July 2014 and will be used to measure all outcomes.

### Sample size

The sample size calculation is based on aggregated practice level antibiotic prescribing. There will be 795 practices participating in the trial, of which 632 practices will be randomised to the intervention group. Each of the eight sub-level experimental units in the intervention group will have 79 practices. This is the required sample size to achieve 80% power (with two-sided alpha of 2.5% allowing for multiple comparisons) to detect a 10% difference in overall antibiotic prescribing between intervention groups. This applies to the comparison between A&F only (n = 316) and A&F with a text-based intervention (n = 316), the comparison between feedback at zero, six, and nine months versus zero and six months only and the comparison between those with and without a Health Board comparator. The sample size has been reduced using the correction described by Borm *et al*. for trials with correlated data [18]. The comparison between the control group (n = 163) and the intervention group (n = 632) will have 80% power to detect a 12% decrease in overall antibiotic prescribing.

The sample size calculation is based on prescribing activity recorded in PRISMS for the 1,799 dentist lists in Scotland known to be prescribing throughout the year ending June 2010. The mean number of antibiotic items prescribed per list was 141.1 with an SD of 140.9. The correlation with the year ending June 2009 is 0.91.

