### Initial and follow-up procedures

All GDPs working in the 632 practices allocated to an intervention group received feedback (*i.e.*, feedback on antibiotic prescribing ± a comparator, ± a text based intervention) at baseline (May 2013) and updated feedback at six months (Nov 2013) (Figure 1). At nine months (February 2014), a further round of feedback will be delivered to GDPs in 50% of practices allocated to an intervention group (Figure 1). All intervention documents will be in paper form and delivered by post (Figure 2). These will be accompanied by a personalised cover letter providing information about the study and contact details for the TRiaDS Programme Office in the event of questions or requests for further information (Additional file 2).

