### Outcomes

All outcomes pertain to cluster level (*i.e.*, dental practices).

The primary outcome is the total number of antibiotic items (from Section 5.1 of the British National Formulary [15]) dispensed per 100 claims over the 12 months from May 2013 to April 2014.

The secondary outcomes are:

1. Total number of Amoxicillin 3 g items dispensed per 100 claims over the 12 months from May 2013 to April 2014 [16].

2. Total number of ‘second-line’ antibiotic items (Clindamycin, Co-amoxiclav, Clarithromycin) [1] dispensed per 100 claims over the 12 months from May 2013 to April 2014.

3. Total defined daily doses of antibiotics [17] (from Section 5.1 of the British National Formulary [15]) dispensed per 100 claims over the 12 months from May 2013 to April 2014.

4. Total defined daily doses of Amoxicillin 3 g dispensed per 100 claims over the 12 months from May 2013 to April 2014.

5. Total defined daily doses of ‘second-line’ antibiotics (Clindamycin, Co-amoxiclav, Clarithromycin) [1] dispensed per 100 claims over the 12 months from May 2013 to April 2014.

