### Data collection and processing

#### Schedule of data collection

MIDAS and PRISMS data are updated routinely by ISD on a monthly basis with a time lag of between two and three months. Updates of data will be received by the TRiaDS Office every month throughout the duration of the trial. Data covering the period up to 31 December 2012 was received in March 2013 and used for the intervention at baseline. Data up to 30 June 2013 was received in September 2013 and used for the six-month intervention (feedback was disseminated on 1 November 2013). Similarly, data up to 30 September 2013 will be used for the nine-month intervention (feedback will be disseminated on 1 February 2014).

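### The feedback-frequency contrast is credited with 80% power for a 10% difference in the 12-month rate, but its arms can differ in only about 3 of those 12 months, so that difference needs roughly a 40% fall in February to April 2014

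*Protocol article*

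**What the plan says.** All places are in the protocol article.

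- **Initial and follow-up procedures:** every intervention practice receives feedback in May and November 2013. The frequency arms then separate: "At nine months (February 2014), a further round of feedback will be delivered to GDPs in 50% of practices allocated to an intervention group".
- **Schedule of data collection:** the date of that third round is fixed: "feedback will be disseminated on 1 February 2014".
- **Outcomes:** the primary outcome is antibiotic items "dispensed per 100 claims over the 12 months from May 2013 to April 2014". All five secondary outcomes use the same window.
- **Statistical analysis:** frequency of feedback is one of the effects to be estimated, by analysis of covariance on the 12-month rate. **Timing and frequency of analysis** allows one principal analysis, on data to 30 April 2014.
- **Sample size:** "This is the required sample size to achieve 80% power", with a "two-sided alpha of 2.5% allowing for multiple comparisons", "to detect a 10% difference in overall antibiotic prescribing between intervention groups". The section applies this to the text contrast, to "the comparison between feedback at zero, six, and nine months versus zero and six months only", and to the health board comparator contrast.

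The Discussion explains why no round was sent at three months. Nowhere does the article mention that the frequency factor starts late, and it gives that factor no separate window or effect size.

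**The concern.** The text and comparator factors act from the baseline mailing, so the whole outcome window is exposed to them. The frequency factor acts only from 1 February 2014. About nine of the twelve months in its outcome precede any difference between its arms. Those months add variation but no signal, and they shrink any real effect to about a quarter of its size. Even so, the plan states one power and one detectable difference for all three factors.

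Frequency is one of the three factorial questions and part of the stated research question. A reader who accepts the 80% figure could take a null 12-month result as good evidence that a third round has no value, when the comparison had little chance of showing a modest effect.

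**Working it through.** **Inputs**, from Sample size unless noted:
- mean 141.1 and SD 140.9 items per dentist list, so CV = 140.9/141.1 = 0.999
- correlation with the previous year, r = 0.91
- 316 v 316 practices: "A&F only (n = 316) and A&F with a text-based intervention (n = 316"). Each level of each factor has 4 × 79 = 316
- two-sided alpha 2.5%, so the critical value is 2.2414
- window 1 May 2013 to 30 April 2014 (Outcomes; Timing and frequency of analysis)
- arms first differ on 1 February 2014 (Schedule of data collection)

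**Step 1: reproduce the plan's figure.** The stated correction for correlated data multiplies the variance by 1 − r² = 1 − 0.91² = 0.1719. The adjusted relative SD is k = 0.999 × √0.1719 = 0.414. For a relative difference d,

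power = Φ(d/k × √(316/2) − 2.2414), plus a negligible opposite tail.

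With d = 0.10: 0.10/0.414 × 12.57 = 3.036, and Φ(3.036 − 2.241) = 78.7%. This agrees with the stated 80% to within rounding. The difference detectable with exactly 80% power is 10.15%. The claim is therefore arithmetically sound for a 10% difference in the full-year outcome.

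**Step 2: share of the window that can differ.** February to April is 3/12 = 0.25 of the months, or 89/365 = 0.244 of the days. I assume items and claims are spread evenly over the year and the third round takes effect at once.

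**Step 3: last-quarter fall needed for a 10% annual difference.** 0.10/0.25 = 40% (0.10/0.244 = 41% by days). If the effect is delayed and only 2.5 months respond, 0.10/(2.5/12) = 48%. If only 2 months respond, 0.10/(2/12) = 60%.

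**Step 4: power of the 12-month contrast, by true last-quarter fall.**

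| Fall, Feb–Apr 2014 | Difference over 12 months | Power |
|---|---|---|
| 10% | 2.5% | 7% |
| 20% | 5.0% | 23% |
| 30% | 7.5% | 51% |
| 40% | 10.0% | 79% |

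For scale, the same section powers the comparison of any feedback with control for a 12% decrease over the full year.

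**Step 5: the alternative window.** If the contrast is analysed on February to April 2014 only, a 10% fall in that quarter is not diluted. The protocol gives no quarterly CV or correlation. Assuming CV 1.0, power for a 10% fall is 32% at r = 0.7, 44% at r = 0.8 and 74% at r = 0.9.

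**The case against.** **The statement is not a numerical error.** It names a detectable difference in the annual rate, it reproduces, and it does not forecast that a third mailing will achieve that difference. This stands. The defect is that the figure is carried unqualified to a factor that acts for a quarter of the window.

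**The absolute powers are uncertain.** The CV and correlation describe annual item counts per dentist list. The analysis uses items per 100 claims aggregated by practice, and dividing by claims may remove variation due to workload. As an assumption only, keeping r = 0.91, a CV of 0.7 gives 12%, 47% and 84% power for last-quarter falls of 10%, 20% and 30%. A CV of 0.5 gives 23%, 79% and 99%. A practice-level correlation below 0.91 would pull the other way. This stands too: the powers in the table are conditional, while the fourfold dilution does not depend on these inputs.

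**The annual window has a rationale.** It compares a year under a two-round and a three-round programme, with one outcome and model throughout. The Discussion also notes that claims are filed at the end of a course of treatment while antibiotics may be dispensed at any time during it, and a short window is more exposed to that mismatch. This supports reporting the 12-month rate as well. It does not support giving this factor the same power as the other two.

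**A stronger reading is tempting:** that a null result is all but certain and the frequency question cannot be answered. The documents do not support it. Even on the plan's own inputs a 30% last-quarter fall has about even odds of detection, and the true practice-level variability is unknown.

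**Conclusion.** The concern holds as a mismatch between one contrast and its outcome window. The stated 80% power for a 10% difference does not carry over to the frequency factor in any useful sense, because it corresponds to about a 40% fall in February to April 2014. That figure rests on even monthly volumes and an immediate effect, and any delay raises it. It also takes the two frequency arms to be treated alike before 1 February 2014. The article supports this, although the cover letter is in an additional file that is not shown.

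On the plan's list-level inputs, power is about 7%, 23% and 51% for last-quarter falls of 10%, 20% and 30%. The supportable conclusion is low power for small to moderate late effects. A reader might infer that the whole factorial analysis is compromised, but the feedback-versus-control, text and comparator contrasts all start at baseline and are unaffected by this point.

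**What to change.** 1. **Sample size:** stop applying the 80%/10% statement to the frequency factor without qualification. State that a 10% difference over 12 months corresponds to about a 40% fall in the last quarter.
2. **Outcomes and Statistical analysis:** before the July 2014 data arrive, pre-specify items per 100 claims from 1 February to 30 April 2014 as the outcome for the frequency contrast. Adjust for the pre-intervention rate and for the May 2013 to January 2014 rate, a period in which both frequency arms were treated alike. Report the 12-month rate for this contrast as well.
3. Keep the 12-month outcome for all other contrasts.
4. **Interpretation:** state that a null 12-month result on frequency does not show that extra feedback adds nothing.

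**Cost:** changes of wording and one further model. The February to April data are already due in July 2014. The three-month rate is noisier and more exposed to the claim and dispensing timing mismatch. Power for a 10% fall would be about 32% to 74% on the assumed inputs (CV 1.0, r 0.7 to 0.9), still below 80%, so the change improves the contrast without restoring the stated power. Longer follow-up of this contrast is optional. It would go beyond the stated 12-month trial and single analysis, and would be subject to data permission.

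### The power statement is labelled practice-level, but its inputs are item counts per dentist list, so it does not describe the primary outcome, a practice-level rate per 100 claims

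*Protocol article*

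**What the plan says.** The Sample size section opens with "The sample size calculation is based on aggregated practice level antibiotic prescribing". It claims "80% power (with two-sided alpha of 2.5% allowing for multiple comparisons"), with 316 practices on each side of every factorial contrast, "to detect a 10% difference in overall antibiotic prescribing between intervention groups". For control (163 practices) against all intervention practices (632) it claims 80% power for a 12% decrease, without restating the alpha. It adds that the sample size was reduced by a published correction for correlated data.

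The planning data come in the second paragraph, and their unit is the dentist list, not the practice. The location and spread are given as follows: "The mean number of antibiotic items prescribed per list was 141.1 with an SD of 140.9". These figures cover 1,799 lists in the year to June 2010. On stability from one year to the next, the article reports a correlation of 0.91 with the preceding year.

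Elsewhere the article fixes the unit and scale of the outcome. Under Outcomes, "All outcomes pertain to cluster level", and the primary outcome is items dispensed per 100 claims over 12 months. Under Statistical analysis, "Outcomes will be aggregated and analysed at the practice level", by ANCOVA on the 12-month rate, adjusting for the pre-intervention rate, practice size and annual number of claims.

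**The concern.** The opening sentence and the planning data cannot describe the same calculation. Under Initial data linkage and processing, a list number identifies a dentist, not a practice. There are two separate mismatches with the primary outcome.

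- **Unit.** The SD is between lists. The analysis uses variation between practices, many of which hold several lists.
- **Scale.** The planning variable is a raw yearly count, which includes how busy each dentist is. The outcome divides by claims. Both the relative spread and the year-to-year correlation may differ on that scale, and a stable workload may itself be part of why the counts correlate at 0.91.

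The correlation matters because it removes 83% of the variance (1 − 0.91² = 0.172). Nothing in the article shows that it holds for a practice-level rate.

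At stake is how a null result is read. These are the only power statements in the article, and the Background describes audit and feedback effects as small to moderate. A reader who sees no difference in a factorial contrast will ask whether a 10% effect was detectable, and the stated figure answers that for a different variable.

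**Working it through.** **Inputs** (Sample size section): mean m = 141.1, SD s = 140.9, so CV = s/m = 0.9986; r = 0.91; two-sided alpha 2.5% (z = 2.2414); power 80% (z = 0.8416); sum of z = 3.0830. I take the cited correction to be the usual ANCOVA factor 1 − r² and use the normal approximation.

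Adjusted SD = 140.9 × √(1 − 0.91²) = 58.42; adjusted CV = 58.42/141.1 = 0.4140.

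**Step 1: the 10% figure, 316 v 316.**
- Detectable difference = 3.0830 × 0.4140 × √(2/316) = 10.15%.
- Power for 10%: 0.10 / (0.4140 × √(2/316)) − 2.2414 = 0.795, which gives 78.7%.
- Required n per side = 2 × 3.0830² × 58.42² / 14.11² = 326. Rounding of r (0.905 to 0.915) gives about 343 down to 309, which covers 316.
- Without the correction, n would be 1,896 per side.

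So the stated 10% is approximately recovered by treating each practice as one list and the endpoint as a raw item count.

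**Step 2: the 12% figure, 163 v 632, same inputs.**
- Detectable difference = 3.0830 × 0.4140 × √(1/163 + 1/632) = 11.2%.
- Power for 12% = 85.5%.

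The stated pairing of 12% with 80% is not reproduced. A smaller alpha would bring it close: two-sided 1.25% gives 12.1%, and 1.67% gives 11.8%. The article states neither.

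**Step 3: how far the unit could matter.** 1,799/795 = 2.26 lists per practice. This is rough, because the lists are from the year ending June 2010 and the practices are those eligible in April 2013. Suppose the practice value is the mean count per list, r stays at 0.91, and the within-practice correlation ρ between lists runs from 0 to 1. Then CV = 0.9986 × √((1 + 1.26ρ)/2.26), which runs from 0.66 to 1.00. The detectable difference is 6.8% to 10.2% for 316 v 316 and 7.5% to 11.2% for 163 v 632. If the practice total is used instead, adding an assumed practice-size CV of 0.5 to 0.8, the ranges are 8.5% to 13.0% and 9.3% to 14.4%.

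**Step 4: how far the scale could matter.** The article gives no CV or correlation for the rate per 100 claims, so these are assumed values. Cells show 316 v 316 / 163 v 632, at two-sided alpha 2.5% and 80% power.

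| CV of practice rate | r = 0.70 | r = 0.80 | r = 0.91 |
|---|---|---|---|
| 0.4 | 7.0% / 7.7% | 5.9% / 6.5% | 4.1% / 4.5% |
| 0.6 | 10.5% / 11.6% | 8.8% / 9.8% | 6.1% / 6.7% |
| 0.8 | 14.0% / 15.5% | 11.8% / 13.0% | 8.1% / 9.0% |
| 1.0 | 17.5% / 19.3% | 14.7% / 16.3% | 10.2% / 11.2% |

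The values fall on both sides of 10% and 12%.

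**The case against.** The strongest reply is that nothing in the trial depended on this calculation. Every eligible practice in Scotland was randomised at once, baseline and six-month feedback had been delivered by December 2013, and the final confidence intervals will use the observed practice-level variance whatever SD was used in planning. That stands, and it is why this is a correction to a stated figure and not to the conduct of the trial.

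A second reply is that list counts are probably a cautious proxy. Averaging over lists lowers the CV, and dividing by claims should lower it further to the extent that items rise with claims. At CV 0.66, r could fall to about 0.79 before the 316 v 316 detectable difference passed 10%; at an assumed CV of 0.5, to about 0.58. The ANCOVA also adjusts for practice size and number of claims, which my formula ignores. This is plausible, but the article does not make the argument, and a weaker correlation on the rate scale could offset it.

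A reader might go further and infer that the trial is underpowered, pointing to the 14.7% and 17.5% cells. The document does not support that. Those cells keep the CV of the raw list counts and lower only the correlation, although the change of scale that could weaken r would also be expected to reduce the CV.

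A reader might also infer that the list data explain both stated differences. They approximately explain the 10%, but not the 12%. Finally, a reader might make something of the planning lists having prescribed all year while practices could enter with up to six months without claims. Those are different variables, and no effect on power can be derived from them.

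**Conclusion.** The point holds as an error in a stated power figure. The label and the inputs contradict each other, and the 10% is approximately what the list-level counts give when practices are counted as n (10.15%, or 78.7% power at 10%). The article therefore gives no detectable difference for its own primary outcome.

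The size of the error is not determinable. Over the assumed grid (CV 0.4 to 1.0, r 0.70 to 0.91) the detectable difference runs from 4.1% to 17.5% for 316 v 316 and from 4.5% to 19.3% for 163 v 632. The direction is unknown and may be favourable. For the control comparison, the stated 12% is more cautious than the 11.2% that the listed inputs give at alpha 2.5%, and the alpha behind it is not stated.

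This rests on two readings. One is that 0.91 is a list-level correlation, which its position straight after the list mean and SD makes the natural reading. The other is that the correction is 1 − r², which the arithmetic supports.

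**What to change.** Before the outcome data, due in July 2014, are analysed:

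1. Compute the mean, SD and year-to-year correlation of items per 100 claims at practice level for the 795 randomised practices, from linked MIDAS/PRISMS data that predate the May 2013 feedback.
2. Restate the detectable differences for 316 v 316 and 163 v 632 from those values.
3. State the alpha used for the control comparison.
4. Correct the opening sentence of the Sample size section to say that list-level item counts were used as a planning proxy.

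The numbers randomised, the outcome, the analysis model and the allocation stay as they are. The cost is a short analysis. The correlation needs two full pre-intervention years, whereas the baseline feedback covered 14 months, so an earlier extract may be required if the team does not already hold one; both databases reach back well before then. The restated figures may be less favourable than those now printed.
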